### **PARTICIPANT SELECTION CRITERIA:**

#### **INCLUSION CRITERIA:**

- Having a histopathological diagnosis of newly diagnosed or relapsed cancer as a reason for hospitalization.
- Being admitted to the Oncology Department of the University Hospital of Salamanca.
- Moderate to severe dependency level: Barthel index score between 20 and 55 points.
- Signing an informed consent authorizing voluntary participation in the study.

#### **EXCLUSION CRITERIA:**

- Cognitive impairment assessed with a Minimental State Examination (MMSE) score below 24 points.
- Hemoglobin levels lower than 10 g/dl.

#### **WITHDRAWAL CRITERIA:**

- Patient's death.
- Disease progression leading to a terminal state.
- Hospitalization at the time of home follow-up.
- Incomplete final assessment.

**Randomization:** Patients in the study population, after the initial interview with the research team and having met the selection criteria, will be randomly assigned to two groups: an intervention group (IG) and a control group (CG). The allocation sequence will be generated by

an independent researcher using the Epidat 4.2 software, with a 1:1 ratio. Participants will be randomized based on the order of their baseline assessment, and the randomization sequence will remain concealed until each patient is assigned to the appropriate group.

**Blinding:** The sequence, randomization, recruitment, and assignment work for each group (experimental or control) will be completed by research staff not involved in the evaluations or interventions, preventing potential biases in the study. Participants will also be blinded and unaware of the group to which they are assigned and the intervention they will receive. External research personnel trained in evaluation procedures will be incorporated to minimize any contamination between groups, ensuring third-party blind assessment. Additionally, the researchers responsible for the statistical analysis will be blinded, increasing the scientific rigor and quality of the study.

**Sample size:** The sample size estimation is based on the potential modification of one of the study's primary variables, the Barthel Index score. A pilot study with a similar population was used as a reference, where the Barthel Index score changed by 5.8 points. With these premises, accepting an alpha risk of 0.05 and a beta risk of 0.2 in a bilateral contrast, 40 subjects in each group are required to detect a difference of at least 5.8 units. A common standard deviation of 8.7 is assumed. A follow-up loss rate of 10% has been estimated. The sample size calculation was performed with the EPIDAT 4.2 software.

---

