### **BASELINE VISIT:**

This will take place just before the patients are discharged from the hospital. Initial data collection will include sociodemographic information, medical history, the presence of comorbidities, and the use of concomitant medications, ensuring that the selection criteria are met. All study variables and questionnaires will be evaluated and completed. At the end of the baseline visit, participants will be randomly assigned to one of the two study groups. For participants included in the experimental group, the structure and organization of the functional rehabilitation program will be explained during a specific visit.

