### **FOLLOW-UP VISITS (15 DAYS) AND FINAL VISIT (1 MONTH):**

These visits will be identical to the baseline evaluation except for the collection of sociodemographic variables, which will only be recorded during the baseline visit. The follow-up visits will take place at the Unidad Docente Asistencial de Terapia Ocupacional (UDATO) of the University of Salamanca.

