The statistical analysis will be conducted by intention-to-treat. Population characteristics will be presented as means and standard deviations for continuous variables and as frequency distributions for qualitative variables. To evaluate comparability at baseline between the two study groups, the Chi-Square test will be used for qualitative variables, and the Student's t-test will be used for comparing means between the two groups. The effect of the intervention on the study variables will be assessed using a repeated measures ANOVA with two study factors (time \* group). Subgroup analyses will be performed considering certain baseline evaluation variables and/or categories, such as age or initial score on the FACT scale. Hypothesis testing will have an alpha risk of 0.05 as the statistical significance threshold. The statistical software used will be SPSS, version 23.0.

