**STATISTICAL ANALYSIS:**

The statistical analysis will be conducted on an intention-to-treat basis. Population characteristics will be presented as means and standard deviations for continuous variables and as frequency distributions for qualitative variables. To assess comparability at baseline between the two study groups, the Chi-Square test will be used for qualitative variables, and the Student's t-test will be used for comparing means between the two groups. The effect of the intervention on the study variables will be evaluated using a repeated measures ANOVA with two study factors (time \* group). Subgroup analyses will be conducted considering certain baseline evaluation variables and/or categories, such as age or initial score on the FACT scale. Hypothesis tests will have an alpha risk of 0.05 as the statistical significance threshold. The statistical software used will be SPSS, version 23.0.

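### Withdrawal criteria that act after randomisation, above all an incomplete final assessment, are not reconciled with the stated intention-to-treat analysis

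*Protocol*

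**What the plan says.** The Withdrawal criteria section of the protocol lists four reasons: "Patient's death", "Disease progression leading to a terminal state", "Hospitalization at the time of home follow-up" and "Incomplete final assessment".

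Allocation precedes all of the events at issue. The Baseline visit section, which places that visit just before discharge, states: "At the end of the baseline visit, participants will be randomly assigned to one of the two study groups".

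The Data analysis section says "The statistical analysis will be conducted by intention-to-treat", and the later Statistical analysis section repeats it: "The statistical analysis will be conducted on an intention-to-treat basis". Both name a repeated measures ANOVA with time and group as factors for the effect of the intervention. Procedures and data collection sets three assessments: baseline, 15 days and one month, the last of them after the intervention.

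On the place of assessment, the protocol says: "The follow-up visits will take place at the Unidad Docente Asistencial de Terapia Ocupacional (UDATO) of the University of Salamanca". Telephone follow-up appears in Work plan and visit structure, but only at 3 and 6 months.

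**The concern.** Intention-to-treat means that every randomised patient counts in the allocated group, whatever happens later. A rule that withdraws a patient because the last assessment is incomplete points the other way. The protocol does not say that withdrawn patients continue to be assessed or that they stay in the analysis.

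The withdrawal reasons are not neutral. The primary outcome is the Barthel Index, and patients enter with scores of 20 to 55. Terminal progression, readmission and being unable to travel to the university unit all tend to go with falling autonomy. Only the experimental arm receives supervised home rehabilitation, assistive devices and home adaptation, so the number or kind of patients removed could plausibly differ by arm. The trial could then report a result for completers under an intention-to-treat label. An analysis plan written later cannot recover Barthel scores that were never collected because the patient had been withdrawn.

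**Working it through.** **1. The texts side by side.** Randomisation takes place at the end of the baseline visit, before discharge. Hospitalisation during home follow-up and an incomplete final assessment can therefore occur only after allocation, and terminal progression during the study month does so too. For progression or readmission, withdrawal could mean no more than stopping the home programme. That reading fails for an incomplete final assessment: the visit follows the intervention, so there is no treatment left to stop. What remains is removal from the data.

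**2. The plan's own sample size.** Inputs from the Sample size paragraph: difference 5.8, SD 8.7, two-sided alpha 0.05, beta 0.2, 10% loss.

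- n per arm = 2 × [8.7 × (1.960 + 0.842) / 5.8]² = 35.3, rounded up to 36.
- 36 / 0.9 = 40 per arm, as stated.

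The figure reproduces. It plans on 36 patients per arm with usable data. That fits a completers' reading but does not prove it, because inflating for loss is also common under intention-to-treat.

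**3. How far removal could move the result.** The protocol gives no removal rates by arm, so these are assumptions: completers change by +5.8 (experimental) and 0 (control), and excluded patients change by m = −15 (range −10 to −20). pE and pC are the excluded fractions in the experimental and control arms.

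(a) Excluded patients change by m in both arms, so they have no treatment effect:

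D = (1 − pE) × 5.8 + pE × m − pC × m

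- 15% vs 5%: 0.85 × 5.8 − 0.15 × 15 + 0.05 × 15 = 4.93 − 2.25 + 0.75 = 3.43 (2.93 to 3.93 over the range of m).
- 5% vs 15%: 5.51 − 0.75 + 2.25 = 7.01 (6.51 to 7.51).
- 10% in each arm: 5.22 − 1.50 + 1.50 = 5.22.

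(b) Excluded experimental patients share the 5.8 benefit:

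D = 5.8 + m × (pE − pC)

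- 15% vs 5%: 5.8 − 15 × 0.10 = 4.3.
- 5% vs 15%: 5.8 + 1.5 = 7.3.
- 10% in each arm: 5.8, no change.

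The gap between (a) and (b) reflects what is assumed about treatment effect in the excluded patients. Version (b) isolates selection.

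**4. A check with no true effect.** Suppose that removal falls on the lowest fraction d of a latent normal variable with correlation ρ to the outcome (SD 8.7). The mean of those kept rises by 8.7 × ρ × φ(c)/(1 − d), where c is the d-quantile of the standard normal and φ its density.

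- d = 10%: 8.7 × 0.1755/0.9 = 1.70ρ.
- d = 30%: 8.7 × 0.3477/0.7 = 4.32ρ.

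With 30% of controls and 10% of experimental patients removed, the spurious difference is −2.62ρ: −0.8 at ρ = 0.3, −1.3 at 0.5 and −2.1 at 0.8. That is 14% to 36% of the 5.8-point target. The sign reverses if the rates do, and equal removal on the same pattern gives no shift.

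**The case against.** Four points deserve weight.

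- **No sentence excludes withdrawn patients from analysis.** Death opens the list, so at least that item simply describes why follow-up ends. Leaving follow-up and being analysed as randomised can coexist if missing values are handled. This stands: a reader might infer that the trial is certain to be analysed on completers only, and the text does not go that far. It does not rescue the incomplete final assessment criterion, which has no other sensible use.
- **Analysis sets and missing-data rules are commonly left to an SAP.** True, and their absence is not the complaint here. The point is a rule the protocol does state, set against a principle it also states.
- **The SPSS procedure is not named.** Dropping a patient with one missing visit is how a classical repeated measures ANOVA behaves, but that this version will be run is an assumption. The Data analysis section also lists two-sample tests, which do not need every visit.
- **The size is illustrative.** The protocol gives no sign of differential loss, and part of the fall to 3.4 comes from assuming no treatment effect in excluded patients. This stands, which is why 4.3 is shown beside it. It would also be tempting to add a loss of power at 20% or 30% dropout. The protocol plans for 10%, and power says nothing about this conflict.

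**Conclusion.** The conflict is real and lies within the protocol. Removal from the analysis is a strong inference rather than a stated rule. It is firmest for the incomplete final assessment and weaker for progression and readmission, which may only mark the end of the home programme. Death properly ends data collection, so listing it is not itself a fault; what is left open is how deaths enter the comparison.

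Bias in the Barthel difference requires that the arms lose different numbers or different kinds of patients. Its direction cannot be known beforehand. Under the assumed figures, a completers' difference of 5.8 corresponds to 3.4 or 4.3 among all randomised when 15% versus 5% are excluded, and to 7.0 or 7.3 when the rates are reversed. Because uncollected scores cannot be recovered and the primary comparison rests on them, this must be fixed in the protocol.

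**What to change.** 1. Delete the incomplete final assessment as a withdrawal criterion and treat it as missing data.
2. Reconcile the remaining criteria with intention-to-treat by separating the end of the intervention from the end of outcome collection. The first is a clinical matter and stays with the investigators. The second should occur only at death or withdrawn consent.
3. Seek the 15-day and one-month Barthel Index from patients who cannot attend the university unit, for example by telephone from the existing blinded assessors.
4. Analyse all randomised patients in their allocated group with a mixed model that uses partial data. Add sensitivity analyses for outcome-related missingness and for deaths.
5. Report deaths, progression, readmissions and missing assessments by arm.

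The cost is a short amendment and some additional calls, since those now planned come only at 3 and 6 months. There are two drawbacks. Some scores will be obtained by telephone rather than in person. The mixed model assumes data missing at random, which is doubtful when deterioration drives the loss, so the sensitivity analyses are needed alongside it.

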## PROCEDURES AND DATA COLLECTION

**Evaluations and study plan:** Participants will be evaluated at three time points during the study: baseline evaluation (at the time of patient referral and before hospital discharge), follow-up evaluation (after 15 days), and final evaluation (one month after the initial evaluation, after the intervention).

The baseline evaluation will be conducted after recruitment and prior to randomization and group assignment. This initial evaluation includes recording independent variables and primary outcome variables, intervening variables, and several objective evaluation tests. After randomization, the corresponding intervention for each group will be carried out. Two subsequent evaluations, the follow-up evaluation and final evaluation, will be performed, during which participants will complete the same objective tests as in the initial evaluation. Results will be reported individually to those who requested to receive their information at the start of the study. All evaluations will be carried out by trained research personnel.

---

### Description of the variables

**Primary outcome variable: Activities of Daily Living (ADL):** ADLs will be assessed using the Barthel Index (BI), whose version has been translated and validated into Spanish (36). The scale assigns a score based on the degree of dependency for performing a series of basic activities, with each item scored between 0 and 15 points. The global range can vary between 0 (completely dependent) and 100 points (completely independent).

**Secondary Variables:**

- **Assessment of associated respiratory pathology or dyspnea:** “Medical Research Council Dyspnea Scale (mMRC)” (17). It allows the patient to quantify their own dyspnea visually and simply, with 5 levels of severity.
- **Assessment of Health-Related Quality of Life (HRQoL):** Quality of life will be assessed using the EuroQol 5-D (EQ-5D) questionnaire, adapted and validated in the Spanish population (39).
- **Pain Assessment:** Pain will be evaluated using the Visual Analog Scale (VAS), widely used for pain assessment. It is represented as a 10 cm line, ranging from 0 = no pain to 10 = worst pain imaginable (39).
- **Physical performance evaluation:** The Short Physical Performance Battery (SPPB), validated in our setting for primary health care, predicts disabilities and adverse events, dependency, institutionalization, and mortality (40).
- **Evaluation of fear of movement related to pain/fatigue:** The Tampa Scale for Kinesiophobia (TSK), developed to assess fear of movement associated with pain, will be applied in its modified 11-item version (TSK-F), validated in cancer patients (41,42).
- **Caregiver burden assessment:** The Zarit Caregiver Burden Scale-Short Version, reduced by Gort A. and colleagues in 2005, consists of 7 Likert scale items scored from 0 to 5. Scores above 17 indicate caregiver strain (18).

## Interventions

To describe the intervention, we must differentiate between the experimental group and the control group. Additionally, we should note that the research team will consist of occupational therapists, nurses, physiotherapists, and medical oncologists. Each professional will be responsible for their specific area of work:

### CONTROL

### GROUP

### (CG):

Intervention for the control group: Delivery of an educational health program booklet prior to hospital discharge.

**Educational Health Program:** At the time of hospital discharge, after the baseline evaluation, instructions and recommendations for maintaining an active and healthy lifestyle will be provided, as will be done in the control group, as part of a health education program. These instructions will primarily address aspects related to the benefits of an active lifestyle and general guidelines to follow, as well as the importance of nutrition and hydration for a healthy life.

Participants will receive the booklet with instructions and recommendations from the health education program, as in the experimental group.

---

### EXPERIMENTAL GROUP (EG):

Intervention for the experimental group: Delivery of an educational health program booklet prior to hospital discharge + prescription of assistive devices and home adaptations + functional rehabilitation.

Patients assigned to the intervention group will undergo a structured and supervised home program consisting of the health education program, combined with a **Functional Rehabilitation and Environmental Adaptation Program**, which will include the prescription of multimodal physical exercise, rehabilitation of activities of daily living (ADLs), and the prescription of

assistive devices and home adaptations. The intervention will last for one month from the time of the baseline evaluation at hospital discharge.

1. **Rehabilitation of Activities of Daily Living (ADLs):** Specific training will be conducted after the evaluation and prior to the patients' discharge from the university hospital. The goal is to identify factors that interfere with the performance of daily living activities. The intervention will consist of three parts: direct intervention on ADLs, teaching Energy Conservation Techniques (ECT), and providing advice on sleep hygiene measures, as outlined in the specific guidelines of the National Comprehensive Cancer Network (NCCN) (45).

The intervention will consist of three parts: I. **Direct intervention on Activities of Daily Living (ADLs):** This will be carried out in the hospital setting and generalized to the patients' daily environments. The aim is to help patients become as autonomous as possible. The first session will take place the day before hospital discharge, with continued supervision throughout the month-long intervention.

II. **Teaching Energy Conservation Techniques (ECT):** These techniques will be based on simplifying activities.

#### **ENERGY CONSERVATION TECHNIQUES FOR PATIENTS (ECT):**

1. Work areas where the activity is carried out should be organized.
2. Work surfaces will be adapted, and objects should be within the patient's reach.
3. When possible, activities should be performed in a seated position; standing will be encouraged as soon as feasible.
4. Impulsive and vigorous movements should be transformed into studied, slow, and harmonious ones.
5. Alternate heavy activities with light ones, incorporating rest periods between them.
6. Balanced periods of activity will be combined with periods of rest.
7. Avoid movements or activities that trigger exertion-induced dyspnea.

#### **Table 18. Energy Conservation Techniques for Cancer Patients (ECT)**

III. **Advice on Sleep Hygiene Measures:** As outlined in the specific guidelines of the National Comprehensive Cancer Network (NCCN).

#### **SLEEP HYGIENE MEASURES FOR CANCER PATIENTS:**

- Maintain as regular a sleep-wake rhythm as possible, particularly the wake-up time.
- Avoid stimulant medications and other substances before sleep.
- Maintain good nocturnal analgesic control, preferably using long-acting analgesics.
- Avoid unnecessary time in bed during the day; for bedridden patients, provide physical and cognitive stimulation throughout the day.
- Minimize nighttime interruptions from noise, medication administration, or other environmental factors.
- Remove unpleasant stimuli, such as clocks, from the bedroom.

- Avoid staying awake in bed trying to sleep; engage in a relaxing activity (e.g., reading) outside of bed until sleepiness occurs.
- Avoid late afternoon naps.
- Use hypnotic medications after proper evaluation of sleep disorders and avoid overuse.

**Table 19. Sleep Hygiene Measures for Cancer Patients**

2. **Prescription of Assistive Devices and Environmental Adaptations:**  
Prior to patient discharge and after the baseline evaluation, the possibility of prescribing assistive devices to promote patient autonomy will be assessed, as well as identifying potential barriers in the home environment that could hinder autonomy after discharge. This will be done on the last day before hospital discharge and in the patient's home "in situ."

## **WORK PLAN AND VISIT STRUCTURE**

Once potential candidates to participate in the study are identified in the Oncology Department of the Complejo Asistencial Universitario de Salamanca (CAUSA), the researchers will conduct an interview to explain the purpose of the study and invite them to sign the informed consent form. Each participant will attend three evaluation visits: a baseline evaluation at the start of the study (before randomization) and two follow-up visits at 15 days and 1 month after the first visit. Each of the three scheduled visits will follow the same structure and last approximately one hour. Additionally, telephone follow-up will be conducted 3 and 6 months after randomization. During these visits, the study variables will be evaluated.

### **BASELINE VISIT:**

This will take place just before the patients are discharged from the hospital. Initial data collection will include sociodemographic information, medical history, the presence of comorbidities, and the use of concomitant medications, ensuring that the selection criteria are met. All study variables and questionnaires will be evaluated and completed. At the end of the baseline visit, participants will be randomly assigned to one of the two study groups. For participants included in the experimental group, the structure and organization of the functional rehabilitation program will be explained during a specific visit.

### **FOLLOW-UP VISITS (15 DAYS) AND FINAL VISIT (1 MONTH):**

These visits will be identical to the baseline evaluation except for the collection of sociodemographic variables, which will only be recorded during the baseline visit. The follow-up visits will take place at the Unidad Docente Asistencial de Terapia Ocupacional (UDATO) of the University of Salamanca.

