## **ETHICAL ASPECTS**

The study will be conducted after obtaining approval from the Ethics Committee for Clinical Research of the Salamanca Health Area, with informed consent from the study subjects and in accordance with the Declaration of Helsinki. Participants will be informed of the project's objectives and the risks and benefits of the procedures that will be performed (informed consent). Confidentiality of the subjects included will be guaranteed at all times in accordance with the provisions of Organic Law 3/2018 of December 5, on the Protection of Personal Data and Guarantee of Digital Rights, as well as Regulation (EU) 2016/679 of the European Parliament and the Council of April 27, 2016 (GDPR), and under the conditions set out in Law 14/2007 on Biomedical Research.

Significant modifications to the protocol (such as changes in evaluation tools, selection criteria modifications, or changes in the interventions) will be immediately communicated to the Ethics Committee.

Since this is a randomized clinical trial, it follows the CONSORT guidelines and has been registered. **TRIAL REGISTRATION:** ClinicalTrials.gov; ID: NCT06035263

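### Falls, hospital admissions and deaths are not planned to be recorded systematically or compared by arm, although the experimental arm exercises at home in patients with Barthel scores of 20 to 55

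*Protocol*

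**What the plan says.** **Outcomes.** Under Description of the variables, the primary outcome is the Barthel Index. The secondary variables are mMRC dyspnea, EQ-5D, pain VAS, SPPB, the 11-item Tampa scale and the short Zarit scale.

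**Visits.** Procedures and Data Collection has the two later evaluations repeat the initial tests. The section on the follow-up and final visits states: "These visits will be identical to the baseline evaluation except for the collection of sociodemographic variables, which will only be recorded during the baseline visit". Medical history, comorbid conditions and current medication are added to the scales in the Baseline Visit section. The Work Plan adds telephone contact at 3 and 6 months and says that the study variables are what is evaluated.

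**Events.** The Withdrawal Criteria list death, progression to a terminal state, an incomplete final assessment and "Hospitalization at the time of home follow-up". In the text available, death, terminal progression and admission during follow-up are given no other role.

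**Treatment.** Inclusion requires a Barthel score of 20 to 55. The Experimental Group section describes multimodal exercise, training in daily activities and home adaptation, supervised throughout the month. The energy conservation list says: "When possible, activities should be performed in a seated position; standing will be encouraged as soon as feasible". Controls receive a health education booklet.

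**Risk.** Ethical Aspects says: "Participants will be informed of the project's objectives and the risks and benefits of the procedures that will be performed". Data Analysis mentions a logistic regression for events of interest, which are not defined.

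**The concern.** The protocol foresees that some patients will die, reach a terminal state or be readmitted within the month, because it writes a rule for each. It uses these events only to withdraw patients, not as outcomes to compare between arms. Falls are not mentioned at all. Yet the two arms differ in physical activity at home, in a population selected for moderate to severe dependency.

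Followed as written, the trial could report a Barthel gain with no planned comparison of falls, admissions or deaths beside it. The section on practical utility expects the results to reach routine care quickly, so readers would want that comparison. A later statistical analysis plan can tabulate data that were collected, but it cannot recover falls that no visit asked about.

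**Working it through.** **1. The plan's own figure.** The Sample size paragraph gives the inputs: "accepting an alpha risk of 0.05 and a beta risk of 0.2 in a bilateral contrast"; "A common standard deviation of 8.7 is assumed"; "A follow-up loss rate of 10% has been estimated". It concludes that "40 subjects in each group are required to detect a difference of at least 5.8 units".

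- n per arm = 2 × (1.96 + 0.842)² × 8.7² / 5.8² = 2 × 7.85 × 2.25 = 35.3, rounded up to 36.
- With 10% loss: 36 / 0.90 = 40.

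The stated 40 per group (80 in total) reproduces. The point does not depend on it, and recording harms would not change it.

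**2. What the written plan would yield for each type of event.**

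| Event | Where it could surface | What is missing |
|---|---|---|
| Fall without admission | Repeated medical history, if the patient mentions it | No variable, no question, no table |
| Admission within the month | Withdrawal reason | Planned and unplanned not separated; no by-arm comparison planned |
| Death or terminal progression within the month | Withdrawal reason | No by-arm comparison planned |
| Admission or death after the month | 3- and 6-month calls | The calls evaluate the study variables, and none of these is an event |
| Gradual worsening | Barthel, SPPB, pain VAS, mMRC | Seen only in patients who are still assessed |

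The follow-up visits take place at the university's occupational therapy unit. No other route is stated for learning what happened to a patient who cannot attend at 15 days or 1 month.

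**3. What 40 per arm could say if events were recorded.**

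- No event in n patients: the one-sided 95% upper bound solves (1 − p)ⁿ = 0.05. For n = 40, 1 − 0.05^(1/40) = 7.2%. For n = 36, it is 8.0%.
- Chance of at least one event in an arm of 40 is 1 − (1 − p)⁴⁰: 33%, 55%, 87% and 99% for true rates of 1%, 2%, 5% and 10%.
- Power for a two-sided 5% comparison of proportions is Φ{[|p₁ − p₂| − 1.96 √(2p̄(1 − p̄)/n)] / √[(p₁(1 − p₁) + p₂(1 − p₂))/n]}. For 10% against 30%: (0.200 − 0.175) / 0.0866 = 0.285, which gives 61%.
- By the same formula: 13% for 5% against 10%, 24% for 10% against 20%, and 89% for 10% against 40%.

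The event rates are assumptions, because the protocol gives none. They show that a safety table in this trial would be descriptive and that only very large differences would be detectable.

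**The case against.** The strongest reply is that the plan is less bare than the outcome list suggests.

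- **Repeated history.** If the follow-up visits repeat baseline, they also repeat medical history, comorbid conditions and medication in both arms. This stands. A reader might infer that the visits collect efficacy scales and nothing else, and the Baseline Visit section does not support that. The repeated history is still no structured event record, and it is missing for patients who do not attend.
- **Withdrawals can be counted.** Staff must identify deaths, terminal progression and admissions to apply the criteria, and every patient has a randomised arm. Nor do the criteria say that data collection stops. This stands too, so it would be too strong to say that the trial cannot show harm. What is missing is the plan to compare, and falls that lead to no admission would not appear among the withdrawals.
- **Supervision and caution.** A reader might picture unsupervised hours of exercise. The Experimental Group section calls the programme supervised throughout, and no hours are stated. The energy conservation list prefers sitting where possible, builds in rest and warns against exertional dyspnea.
- **Reporting bias.** Closer contact with the experimental arm might suggest biased spontaneous reports. The protocol describes no spontaneous reporting system, so such a bias is conjecture.
- **Text not seen.** Part of the protocol between Ethical Aspects and Ethical Standards was not available, and safety wording there cannot be excluded. The outcome list and visit content are available, and they contain no harm variable.
- **Small sample.** Forty per arm could not settle whether the programme harms. That is true, and it is why the request is for counts rather than a test.

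**Conclusion.** The point holds as an omission in what the protocol fixes. In the text available, no fall or adverse-event variable is set, follow-up visits repeat baseline, and death, terminal progression and hospitalization serve only as withdrawal reasons. Harms are therefore not planned to be recorded systematically or compared by arm. The documents do not show that the programme is harmful, that it is unsupervised, or that no information on harm could be assembled afterwards.

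It concerns all 80 patients but not the sample size or the primary analysis. It rests on two assumptions: that the part not seen adds no safety outcome, and that the outcome list is complete. It is a cheap improvement that should be made, and at this sample size its yield is descriptive.

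**What to change.** Add to the Secondary Variables a descriptive safety outcome: falls, unplanned hospital admissions and deaths from randomisation.

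- Ask for it with the same scripted questions in both arms at day 15, month 1 and the 3- and 6-month calls already planned.
- Leave out any question that reveals allocation to the blinded assessors. In particular, do not ask whether an event was related to a programme session, which would also have no meaning for controls.
- Check admissions and deaths against the records of the recruiting hospital.
- State that collection continues after any withdrawal event.
- Report the number of events, and of patients with at least one event, by randomised arm, without a hypothesis test.

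Cost: a few minutes per contact, one records check at a single hospital and one table. No visit is added, and treatment and the 40 per group stay as they are. Admissions elsewhere would rest on the scripted questions alone.
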